#### The intervention

The intervention consisted of three components: a one-day training for all participant GPs and RCs, a standardized work procedure for GPs and RCs to follow after training, and the possibility to seek clinical advice from specialist physicians in the research group. The design of the intervention was guided by occupational therapy theory, where occupational performance is regarded as the outcome of a continuous interaction between the person (P), the environment (E) and the occupation (work tasks) (O) [30]. The PEO-model suggests that in order to improve occupational performance, therapists must direct their interventions not only to the individual, but also to the individual’s environment and occupation. In rehabilitation, therapists can assist in for example the adjustment of work tasks, regulation of spare time activities, and modification of the work environment so that the employee can keep work capacity despite physical or mental symptoms and impairments. This requires a shift away from a biomedical perspective to a more holistic approach which takes the patient’s situation into consideration.

In order to enhance knowledge about the relationship between work; stress-related disorders; work capacity and RTW among GPs and RCs, a one day’s training was compulsory for the participants in the intervention group. Lectures and workshops were conducted by researchers who are also experienced clinicians (physicians, psychologists and occupational therapists). The participants were taught both *why* and *how* the employer can be involved at an early stage in the rehabilitation of patients with stress-related disorders. The training day was offered at six occasions from November 2016 to September 2017. GPs (n=66) and RCs (n=13) from the eleven intervention centers underwent training.

The intervention’s central component was a standardized procedure of four steps involving the patient, the GP, the RC and the patient’s employer. This procedure was based on the clinical experience from twelve years of treating patients with exhaustion disorder at the Institute of Stress Medicine [31], and adapted to the primary health care setting, in dialogue with GPs and RCs prior to the intervention. Ordinary medical and psychological treatment and rehabilitation (TAU) was conducted parallel to this procedure.

When a GP had identified a patient for inclusion (step one), the RC set up a meeting with the patient. During this meeting, the RCs informed the patient about the study and collected his or her written consent. The patient filled out a questionnaire containing questions on background characteristics, occupation, symptoms, work stressors and private life stressors, work ability, RTW self-efficacy, employer activities, RTW motivation, and general health (see Table 2). The questionnaire took about 30 minutes to fill in. Patients declining participation were asked to fill in their year of birth, gender and occupation. The RC then used the questionnaire to interview the patient for about one hour (step two), scanned the questionnaire to the medical journal, and provided the GP with a summary. In the next step (step three), the RC called the patient´s employer and filled out a form containing questions about the employer’s view on the situation before and after the patient’s sick-leave, and about the employer’s readiness for the patient’s RTW. This form was also scanned to the medical journal, and the GP was provided with a summary. The procedure ended with a meeting between the RC, the GP, the patient and the employer to set up a plan for RTW (step four). After this final step, the RC filled out a checklist about protocol adherence. All forms and questionnaires also served as research data, and were collected by the researchers.

**Table 2 Tab2:** Content of the patient questionnaire

Item	Label	Questions & references
Q 1-8	Background characteristics	-
Q 9-12	Exhaustion disorder	Questions from Glise et al. [32] on self-reported exhaustion (s-UMS)
Q 13-50	Work stressors	Items from the Work Stress Questionnaire (WSQ) [33]; Job Control Questionnaire (JCQ) [34]; the General Nordic Questionnaire for Psychological and Social Factors at Work (QPS Nordic 34+) [35]; and the Copenhagen Psychosocial Questionnaire (COPSOQ II) [36]
Q 51-53	Work ability	Items from the Work Ability Index (WAI) [37]
Q 54	RTW- self efficacy	Questions from Lagerveld et al. 2010 [38] on return to work self-efficacy (RTW-SE)
Q 55-57	Employer activities before sick-leave	Questions from the method Workplace Dialogue for Return to Work [21, 39]
Q 58-60	RTW motivation	Item on RTW motivation in van Oostrom et al. 2010 [40]
Q 61a-n	Life stressors	Questions from Hasselberg et al. 2014 [41]
Q 62-75	Symptoms of anxiety and depression	Items from the Hospital Anxiety and Depression scale (HAD) [42]
Q 76-93	Symptoms of burnout	Items from the Shirom-Melamed Burnout Questionnaire (SMBQ) [43]
Q 94	General health	One item from the SF-36 scale [44]

During the intervention, all participants in the intervention group were offered clinical advice by phone or e-mail from the specialist physicians at the Institute of Stress Medicine.

The control group started inclusion at the same day as the first training day for the intervention group, in November 2016. After providing their informed consent, patients at the control centers received TAU, which can include for example medical treatment, and psychological therapy. At some of the control centers, TAU also included RC getting in contact with employers, but normally this is done long into the sick-leave period.

Inclusion of patients lasted from November 2016 until the end of January 2018. The recruitment period was extended by six months compared to the original plan. During the intervention, the researchers revisited all centers for at least one occasion to encourage GPs and RCs to recruit patients. News letters from the project were regularly sent to all PHCC managers and RCs at both intervention and control centers. Also, research assistants contacted all RCs once a month by phone for follow-up.

#### Sample size

In all 135 patients were recruited; 69 to the control group and 63 to the intervention group (see Fig. 1). Depending on the proportion of patients on sick-leave at three, six and twelve months after inclusion, power will vary between 41 % and 74 % (based on the assumption that the prevalence of sick-leave in the control group fluctuates between 20 % and 95 % and with an estimated difference between the groups of 15 % [45]; a two-sided test and a statistical significance of p < 0.05). There was a substantial variation in the number of recruited patients per PHCC.

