**Methods:**

Twenty-two primary care centers were randomized to either intervention or control group. At the intervention centers, physicians and rehabilitation coordinators underwent training, providing them with both knowledge and practical tools to involve the employer in rehabilitation. At the patient level, employed patients with an ICD-10 F43 diagnosis were eligible for participation (*n*=132). Difference in proportion of patients on full- or part-time sick leave at three, six and 12 months after inclusion will be investigated. Register data, logbooks and interviews with coordinators and physicians at both intervention and control centers will be used for process evaluation.

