#### Outcome measurements and statistical analyses

The primary outcome of the RCT is RTW. We will analyze the difference between cases and controls in proportion of patients on full- or part-time sick leave at three, six and 12 months after inclusion. We will use data from the Swedish Social Insurance Agency’s Micro Database for Analyzing Social insurance (MiDAS) where all sick-leaves exceeding two weeks are registered. The intention to treat principle will be followed.

The intervention is designed to facilitate for the caregiver to involve the employer in rehabilitation and strengthen the patient’s RTW-SE, but whether these mechanisms are triggered or not will depend on circumstances among patients, employers as well as the caregivers, i.e it will depend on contextual factors [46]. For example, the effect of the intervention on RTW might depend on the patient’s symptom severity, the employer’s readiness for work adaptation, or on the caregivers’ adherence to the protocol. In order to conduct sub-group analysis within the intervention group, a follow-up questionnaire is sent to the patients’ home address by mail at six and 12 months after inclusion. In addition to questions about the rehabilitation process, the questionnaire contains the same items as the baseline measurement. For example we will explore how gender, age, occupation, symptom severity, employer activities and RTW motivation affect RTW.

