## Discussion

Given that patients with stress related disorders constitute the largest and fastest increasing group in the sick-leave statistics in Sweden, there is an urgent need to come up with methods to stop this development. Most of these patients get their sickness certificate issued by a GP in the primary health care system. Although current evidence of how to enhance RTW for CMD patients, including stress-related disorders, is yet inconclusive, many recent reviews point to that employer involvement early on in the process might be an efficient way to reduce sick-leave. However, time constraints and uncertainties about the relationships between work and stress hinder many GPs to involve the employer. RCs have been introduced into Swedish primary health care to support the patient in the RTW process through coordination between different stakeholders. This opens a window of opportunity to develop new procedures and tools. This RCT was designed to contribute to knowledge about how procedures of cooperation between GPs and RCs can be organized to facilitate employer involvement and reduce time to RTW among patients suffering from work related stress. Despite considerable efforts to encourage and support GPs and RCs at the participating centers, it turned out to be difficult to recruit patients. Unless the impact of the intervention on RTW is substantial, it will be difficult to detect a difference in RTW between the intervention and control group with the current sample size (*n*= 132).

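### The Sample size section gives 135 recruited patients, but its own split of 69 and 63 adds to 132, the total used elsewhere

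*Protocol article*

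**What the plan says.** The Sample size section reports completed recruitment: "In all 135 patients were recruited; 69 to the control group and 63 to the intervention group". It refers to Fig. 1, the flow chart, and then gives the power for this sample: "power will vary between 41 % and 74" per cent. That range assumes control-group sick-leave prevalence between 20 % and 95 %, a 15 % difference between groups, and a two-sided test at 0.05.

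Two other places give a total. The Methods part of the abstract says that employed patients with an F43 diagnosis "were eligible for participation (*n*=132"). The Discussion comments on the difficulty of detecting a difference "with the current sample size (*n*= 132").

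The section on outcome measurements and statistical analyses adds: "The intention to treat principle will be followed". The primary outcome comes from the Social Insurance Agency's MiDAS register.

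**The concern.** A total and its breakdown stand in one sentence and do not agree. The number recruited is an exact count, and it is the base for the power statement and for the proportions to be compared at three, six and 12 months.

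The sentence can be read in two ways. Either 135 is a slip for 132, or 135 patients were recruited and three do not appear in either arm. The first needs only a correction. The second would need an account of the three, because the plan commits to intention to treat. Centres were randomised before patients were recruited, and staff knew their allocation. The register outcome also does not depend on patients returning a questionnaire. A reader of this sentence alone cannot tell which reading applies.

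**Working it through.** **1. The count**

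Inputs, all from the Sample size section: stated total 135, control 69, intervention 63.

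- Sum of arms: 69 + 63 = 132.
- Gap: 135 − 132 = 3 patients.
- Relative size: 3 / 135 = 2.2 %.

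**2. The three places side by side**

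| Place | Total |
|---|---|
| Sample size, stated total | 135 |
| Sample size, sum of arms | 132 |
| Abstract, Methods | 132 |
| Discussion | 132 |

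Only the stated total of 135 disagrees with the rest.

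**3. Does the stated power range identify the right total?**

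Assumption: the 15 % difference is an absolute reduction, so p2 = p1 − 0.15. The article does not name its formula. I used the normal approximation with a pooled variance under the null hypothesis:

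power = Φ{ [0.15 − 1.96 × SE0] / SE1 }, where

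- SE0 = √[ p̄(1 − p̄)(1/n1 + 1/n2) ], with p̄ the mean of p1 and p2 weighted by arm size
- SE1 = √[ p1(1 − p1)/n1 + p2(1 − p2)/n2 ]

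Worked example with 69 and 63 at 20 % against 5 %:

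- p̄ = (69 × 0.20 + 63 × 0.05) / 132 = 0.1284
- SE0 = 0.0583 and SE1 = 0.0554
- power = Φ[(0.15 − 1.96 × 0.0583) / 0.0554] = 74.0 %

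The same formula over the stated prevalence range, for the printed arms and for three illustrative splits that total 135:

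| Control / intervention | Total | Lowest power (near 57.5 %) | At 20 % | At 95 % |
|---|---|---|---|---|
| 69 / 63 | 132 | 40.5 % | 74.0 % | 75.0 % |
| 72 / 63 | 135 | 41.2 % | 74.7 % | 76.1 % |
| 69 / 66 | 135 | 41.3 % | 75.3 % | 75.8 % |
| 67.5 / 67.5 | 135 | 41.3 % | 75.6 % | 75.6 % |

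The article's range of 41 % to 74 % is reproduced to within about 1 point from 69 and 63. It does not discriminate. The lower figure of 41 % is slightly nearer to the splits of 135. The upper figure of 74 % is matched by 132 at 20 % prevalence, but 132 gives 75 % at the 95 % end.

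**4. Effect on power**

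Going from 132 to 135 raises the lowest power by 0.7 to 0.8 points, power at 20 % prevalence by 0.7 to 1.6 points, and power at 95 % by 0.6 to 1.1 points. That is about 1 to 2 points at most.

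**The case against.** The strongest reply is that this is a misprint with no bearing on the analysis. The arm sizes are stated once and not contradicted, the abstract and Discussion agree with their sum, and only one number stands alone. The sentence also refers to Fig. 1, which is where recruited patients who later withdrew or proved ineligible would be accounted for. That figure is not in the text available, so it cannot be said that an account of the three is lacking. Most of this stands, and it is why the point is a minor one. It does not remove the contradiction: whatever Fig. 1 shows, the sentence presents 69 and 63 as the breakdown of all 135.

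A reader might go further in three directions, none of which the article supports.

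- **That the intention-to-treat denominator is unsettled, or that patients were dropped after allocation was known.** No text shows an exclusion. A misprint, withdrawn consent or ineligibility found later would each fit the sentence, and the stated principle is not departed from anywhere.
- **That the power range proves 132.** The table above shows that it fits both totals about equally well.
- **That a bias of a definite size follows.** Adding three patients with the same outcome to the 63 would shift that arm's proportion by up to 3/66 × 0.5 = 2.3 points from a base of 50 %, and by up to 3/66 × 0.95 = 4.3 points from a base of 5 %. The arm, the outcomes and the base proportion are all unknown, so no single figure can be defended.

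**Conclusion.** The total of 135 is wrong as written, because it is inconsistent with its own split by three patients. The probable intended number is 132, on the strength of the arm sizes, the abstract and the Discussion; the power figures add nothing to that inference. This is a small reporting error in a number that the trial relies on. It leaves the trial's power essentially unchanged, and it is not evidence of improper exclusion. The arithmetic of the count rests on no assumption. The power comparison assumes an absolute 15-point reduction, the normal approximation above, and illustrative splits for a total of 135.

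**What to change.** Check the recruitment records and Fig. 1, then do one of the following.

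- **If 132 is right:** replace 135 with 132 in the Sample size section. Nothing else changes.
- **If 135 patients did consent:** reword the sentence so that the total, the arms and the flow chart agree. In line with the stated intention-to-treat principle, analyse the three from register data in the arm of their centre, unless they withdrew consent for data use or were ineligible on facts that predate inclusion. Bring the abstract and the Discussion into line with the resulting number.

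The cost is one corrected sentence. In the second case it is also up to three added register records and the matching edits to the other two totals.

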### The RCT

#### Target group, recruitment and randomization

The target group for the intervention was GPs and RCs at the included PHCCs, and by extension their patients, sick-listed from work due to a stress-related diagnosis. The recruitment of PHCCs took place between January and October 2016. A first request to the PHCCs to participate were communicated by telephone calls, e-mails and personal meetings with PHCC managers throughout the Västra Götaland region. In order to attain diversity in terms of geographical location, public or private ownership, center size, and the socioeconomic conditions of the area, interested centers were checked against regional register data. We also considered the number of patients with a F43 diagnosis at the center during one year (2015), the center’s involvement in other research projects, and the extent of RC resources at the center.

Out of the 30 public and private PHCCs that were invited to participate, 22 accepted; 15 public and seven private centers. Managers accepted the center’s commitment by signing a contract with the researchers. Managers were asked to make sure that the entire staff agreed to the center’s participation in the study before signing the contract. The researchers visited each center to inform the staff about the study prior to commitment. PHCCs were offered economic compensation for recruited patients; € 50 per patient in the control group and € 100 per patient in the intervention group. Also, all centers were offered the one day training program, however they were informed that if allocated to the control group, they would have to wait until all patients were recruited to the study.

Based on similar characteristics in register data, we matched centers in pairs. From each pair, one center was randomly selected to the intervention group and the other one to the control group. The staff of the participant centers were all aware about their allocation in the RCT, blinding was not possible in this study.

Employed patients with a F43 diagnosis as the main diagnosis, getting their sickness certification renewed were eligible for participation. Excluded were patients with post-traumatic stress disorder, F43.1. Patients who did not read or speak Swedish, and patients who have had a sick-leave period of more than 60 subsequent days during the past three years before inclusion were not asked to participate.

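### The stated power of 41 to 74 % is that of a patient-randomised trial; 22 centres were randomised, so this design has less

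*Protocol article*

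**What the plan says.** The unit of randomisation is clear. The Abstract (Methods) states: "Twenty-two primary care centers were randomized to either intervention or control group". The section on target group, recruitment and randomization adds that centres were matched in pairs on register data, and then: "From each pair, one center was randomly selected to the intervention group and the other one to the control group".

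The Sample size section works from patient counts, "69 to the control group and 63 to the intervention group", and states that "power will vary between 41 % and 74" per cent. It lists three assumptions:

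- control prevalence: "the prevalence of sick-leave in the control group fluctuates between 20 % and 95" per cent;
- effect: "an estimated difference between the groups of 15" per cent;
- test: "a two-sided test and a statistical significance of p < 0.05".

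The section then closes with: "There was a substantial variation in the number of recruited patients per PHCC". No ICC, design effect or number of centres appears among the assumptions. The first paragraph of the Discussion warns that only a substantial effect is likely to be detected, and attributes this to the sample of 132 patients.

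**The concern.** Patients of one centre share the same physicians, coordinator, sick-listing habits and local labour market, so their outcomes tend to be correlated. When whole centres are randomised, that correlation inflates the variance of the difference between arms, and unequal centre sizes inflate it further. The Discussion itself expects implementation to depend on routines, cooperation and workload at each centre, which makes an ICC of exactly zero hard to defend.

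The power range is the article's only numerical statement of what the trial can detect. If it is computed as though patients had been randomised one by one, a reader of a null result will credit the trial with more ability to find a 15-point difference than it had.

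**Working it through.** **Inputs from the article.** 69 control and 63 intervention patients; difference 0.15; two-sided 5 % level; control prevalence 0.20 to 0.95; 22 centres, 11 per arm. The arms sum to 132, the total in the Abstract and Discussion. The Sample size section also prints 135, which does not affect what follows. The difference is taken as a reduction, the intended direction; a rise of 15 points from 95 % is impossible.

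**Step 1: reproduce the stated range without clustering.** Pooled-variance test of two proportions:

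power = Φ[(0.15 − 1.96·s0)/s1], with s0 = √{p̄(1−p̄)(1/69 + 1/63)} and s1 = √{p1(1−p1)/69 + p2(1−p2)/63}.

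- 20 % vs 5 %: p̄ = (69×0.20 + 63×0.05)/132 = 0.128; s0 = 0.0583; s1 = 0.0554; power = Φ(0.645) = 74.0 %.
- 50 % vs 35 %: power = 41.2 %.
- Minimum, at about 57 % vs 42 %: s0 = 0.0871; s1 = 0.0861; power = Φ(−0.241) = 40.5 %.
- 95 % vs 80 %: s0 = 0.0569; s1 = 0.0568; power = 75.0 %.

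Both printed ends, 41 and 74 %, are matched to within about one point with a design effect of 1. The figure is therefore an unadjusted one, not a cluster-adjusted figure whose details were cut from the article.

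**Step 2: put the clustering back.** Mean centre size is m = 132/22 = 6. For unequal clusters,

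DE = 1 + [(CV² + 1)·m − 1]·ICC,

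and both arm sizes are divided by DE. The article gives neither ICC nor CV, so both are assumptions here. For example, with CV 0.6 and ICC 0.05: DE = 1 + (1.36×6 − 1)×0.05 = 1.358, and effective N = 132/1.358 = 97.

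| CV of size | ICC | DE | Effective N | Power, control 20 % | Power, control 57.5 % (about the minimum) | Power, control 95 % |
|---|---|---|---|---|---|---|
| – | 0 | 1.00 | 132 | 74 % | 40 % | 75 % |
| 0 | 0.01 | 1.05 | 126 | 72 % | 39 % | 73 % |
| 0 | 0.05 | 1.25 | 106 | 64 % | 34 % | 65 % |
| 0 | 0.10 | 1.50 | 88 | 56 % | 29 % | 58 % |
| 0.6 | 0.02 | 1.14 | 115 | 68 % | 36 % | 69 % |
| 0.6 | 0.05 | 1.36 | 97 | 60 % | 31 % | 62 % |
| 0.6 | 0.10 | 1.72 | 77 | 50 % | 26 % | 52 % |
| 1.0 | 0.05 | 1.55 | 85 | 55 % | 28 % | 56 % |
| 1.0 | 0.10 | 2.10 | 63 | 42 % | 22 % | 44 % |

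**Step 3: few randomised units.** The table uses a normal reference. With 22 centres or 11 pairs, a t reference with 20 or 10 degrees of freedom is more realistic. At CV 0.7 and ICC 0.05, the normal reference gives 31 to 61 %. A noncentral t with unpooled variance gives about 29 to 59 % (20 df) or 27 to 54 % (10 df).

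**Step 4: precision.** Near 50 % prevalence the 95 % half-width without clustering is 1.96·√{0.25(1/69 + 1/63)} = 17 points, already more than the 15-point target. At DE 1.36 it is 17.1×√1.358 = 20 points.

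**The case against.** The strongest reply is that nothing in the trial's conduct hangs on this number. Recruitment had closed, the power was computed from patients already enrolled, and it sets no sample size, stopping rule or analysis. The whole printed range is below 80 % and the Discussion says openly that detection will be difficult, so a reader already expects a null result to be inconclusive. That is fair, and it limits the consequence: the correction lowers a power that was already low and does not reverse a conclusion. But the Discussion attributes the limit to patient numbers alone, and a candid tone does not make the printed figure right.

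The second reply is that the size of the error is unknown. This also stands. With equal centres and ICC 0.01 the loss is only about 2 points before any degrees-of-freedom correction. It grows only with assumptions that the article neither supplies nor rules out, although its remark on uneven recruitment makes equal centres a best case.

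The third is that centres were matched in pairs, which may recover some between-centre variance, while an analysis of 11 pairs costs degrees of freedom. The net effect cannot be worked out from the article. It claims no gain from matching, and its figure reproduces without one.

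Finally, under its own inputs the range is computed correctly. The fault lies in applying an individually randomised formula to randomised centres.

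**Conclusion.** The concern holds. The printed 41 to 74 % is the power for 132 independently randomised patients, and this trial randomised 22 centres. That conclusion needs no assumed ICC, because the figure reproduces with a design effect of 1.

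The size of the overstatement does depend on assumptions. It runs from about 2 points (ICC 0.01, equal centres) to roughly 10 to 14 points (ICC 0.05, CV 0.6: 31 to 62 % against a reproduced 40 to 75 %). At ICC 0.10 with CV 0.6, power is 26 to 52 %. These figures ignore any gain from matching and the loss from few degrees of freedom. The statement needs correcting; the trial's conduct does not.

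**What to change.** 1. Recalculate the power from the recruited numbers in each centre, which the sponsor holds, with DE = 1 + [(CV² + 1)m − 1]·ICC over ICC 0.01 to 0.10. Report the range with the ICC and CV used.
2. Keep 41 to 74 % only if it is labelled as the upper bound that ignores clustering.
3. State whether the recalculation takes account of the pair matching, and which degrees of freedom it uses.
4. Carry the corrected range into the Discussion, so that the limit on detection is tied to the 22 randomised centres as well as to the 132 patients.

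The cost is one calculation and a reworded paragraph, with no extra patients or data. The stated power becomes less favourable.
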